## Abstract

**Background:**

South Africa has a high and rising prevalence of hypertension. Many affected individuals are not using medication, and few have controlled blood pressure. Until recently, primary care clinics focused on maternal and child health and management of acute conditions, but new government initiatives have shifted the focus to chronic diseases, including HIV/AIDS and hypertension.

**Methods/Design:**

The Nkateko trial will test the effectiveness of clinic-based lay health workers (LHWs) in supporting hypertension management. It is a pragmatic, cluster randomised controlled trial based in the Agincourt subdistrict of northeast South Africa, and it is underpinned by long-term health and demographic surveillance. Eight primary care facilities, with their catchment communities, are randomised to usual care or the addition of LHWs focused on chronic care. All clinics (intervention and control) will be provided with a clerk to collect information on clinic attendees and will match them to preexisting surveillance records. Intervention clinics will have LHWs working alongside nursing staff and focusing on health care for people with chronic conditions, particularly hypertension. The LHWs will be supported by an implementation manager, who will work with clinic staff to develop the most effective role for the LHWs. Control clinics will continue to provide usual care. The primary outcome will be the change between two population surveys conducted before and after the intervention in the proportion of the population with uncontrolled hypertension and a risk profile indicating at least moderate risk of cardiovascular disease. A process evaluation will be based on a realist approach using patient exit interviews, clinic observations and interviews with health professionals, LHWs and patients to document the intervention and its implementation.

**Discussion:**

There are challenges in the design of this trial. Assessing change through population surveys may reduce measurable effects; however, we feel this is appropriate because we aim to attract those who currently do not use clinics, and we hope to improve care for clinic users. Clinics were randomised at an open meeting because we were concerned that a remote process of randomisation would not be trusted by the community. We are constantly working to achieve an effective balance between the intervention and process evaluations.

**Trial registration:**

ISRCTN12128227 (registered 5 March 2014)

**Electronic supplementary material:**

The online version of this article (doi:10.1186/1745-6215-15-435) contains supplementary material, which is available to authorized users.

## Background

There is a complex epidemiological and demographic transition underway in sub-Saharan Africa. The HIV/AIDS epidemic, which has affected a large proportion of the population and caused a dramatic decrease in life expectancy, coexists with an ageing population and an increase in the prevalence of noncommunicable diseases. It is expected that the proportion of the population 60 years of age and older will increase almost threefold by 2025 compared to 1985 data [1]. At the same time, partly due to this demographic shift, South Africa has a high and rising prevalence of hypertension [2, 3]. Hypertension currently affects around 40% of the adult population in the Agincourt subdistrict, a rural area covered by the Agincourt Health and Demographic Surveillance System (HDSS) (unpublished data; [name], [name] see also [4]. In low-resource rural settings, fewer than half of individuals affected by hypertension are aware that they have hypertension, and fewer than 10% achieve appropriate blood pressure levels [5]. There is marked variation in the management of hypertension and other chronic diseases, owing to poor functioning of primary care services, which have historically been focused on maternal and child health and the management of acute illness rather than chronic conditions. Adherence to medication is suboptimal; long-term patient retention is low; and little attention is paid to potential comorbidities [1].

South Africa also has the highest prevalence of HIV/AIDS in the world [6]. The country’s antiretroviral treatment programme is the largest worldwide, and it has seen recent notable increases in coverage [7]. Substantial knowledge has been generated on adherence support, tracing defaulters and enabling patient participation through treatment literacy and patient support groups [8]. This knowledge and experience may potentially be transferable to the management of hypertension, for which the same type of health care intervention may be equally effective in addressing the escalating burden. Treatment of HIV and tuberculosis relies heavily on lay health workers to support patient adherence. In South Africa, lay health workers have successfully (1) provided pre- and posttesting and adherence counselling, (2) assisted patients in navigating their engagement with health staff and (3) helped in tracing defaulters [9–12].

The development of this trial has been informed by the experience of the antiretroviral service and guided by the Wagner conceptual framework for chronic disease care, which emphasise the need for productive interactions between patients, providers and the broader health system [13]. Effective chronic disease care requires a reliable drug supply, longitudinal patient records to monitor care over time and adequately staffed clinics. It is also important that patients have sufficient self-efficacy to manage their illness with support from their social network. In an area such as the Agincourt subdistrict, where more than 90% of all adults have access to a mobile phone, text messaging could be used to improve medication adherence and health-related behaviour modification. There is evidence from a systematic review that text messaging was well accepted and showed early efficacy in most studies by improving medication adherence and health-related behaviour modification [14].

A recent national Department of Health initiative has sought to implement an integrated chronic disease management (ICDM) programme in 50 selected clinics in 3 provinces [15]. The aim of the ICDM programme is to strengthen chronic care by providing additional nurse training, equipment audit and replacement, improved drug supply, reorganised patient flow to allow separate management of chronic diseases and reduction of waiting times, advanced booking, and prepacked medication. The ICDM programme is already operational to a varying extent in the eight clinics in which this trial is being implemented.

Process evaluations are an important addition to randomised trials; they allow better understanding of the causal processes which may facilitate or obstruct change and help to inform the interpretation of outcomes [16, 17]. This is particularly important in a complex trial such as this one, where the interaction between the lay health workers, health care professionals, patients and the wider community is likely to be many-layered and where the interaction between the communities and the primary care clinics that serve them is poorly understood.

## Methods/Design

The full version of the study protocol is available at http://www.chp.ac.za/research/Nkateko/Pages/default.aspx.

### Research hypothesis and objectives

The hypothesis is that the introduction of lay health workers to assist nurses with the management of patients with chronic diseases in rural primary care clinics will improve population-level management of hypertension by improving diagnosis, retention in care and adherence to treatment by individuals with hypertension.

The following are our research objectives:To compare the effectiveness of clinic-based lay health workers to ‘usual care’ in improving the management of hypertension (including access to care, adherence to treatment, and management) in rural South AfricaTo conduct a realist evaluation to understand the patient, intervention, implementation, health care system and community barriers and facilitators that explain patient outcomes in the intervention and ‘usual care’ clinicsTo contribute specific recommendations to strengthen policy and practice in similar rural settings of South Africa and southern Africa.

### Study design

The Nkateko trial is a cluster randomised controlled trial comprising eight clusters each of which consists of a primary health care facility and the community it serves, including residents in a defined catchment area within the Agincourt subdistrict. Figure 1 shows a schematic representation of the trial.

**Figure 1 Fig1:**
[figure not shown]
**Design of the Nkateko trial.** HDSS, Agincourt Health and Demographic Surveillance System; LHW, Lay health worker.

In the trial, we are testing a health service intervention which involves placing lay health workers in four intervention clinics. The lay health workers will assist clinic nurses with the management of patients with chronic diseases. The outcome of the study will be evaluated by using two population-based, random sample, cross-sectional surveys, one at baseline and one at the conclusion of the intervention.

The study has been approved by the Committee for Research on Human Subjects (Medical), the University of the Witwatersrand (reference M130347, M130754, M130964), the Biomedical Research Ethics Committee at the University of Warwick (reference REGO-2013-062, REGO-2013-203, REGO-2013-562) and the Mpumalanga Province Research and Ethics Committee (dates of letters: 7 June 2013, 18 September 2013, 6 November 2013). This cluster randomised trial is a type A trial as defined in the 2002 Medical Research Council (MRC) document on cluster randomised trials [18]. The decision to consent to organisational change in a clinic cannot depend on the consent of users of the clinic. Consent has been obtained from the national, provincial and district authorities, and discussion of implementation within each clinic has taken place in partnership with the clinic staff. We have put notices in all clinics explaining that the clinic is being observed. Individual informed consent is obtained from each participant who is individually approached. This includes all clinic patients who allow their clinical data to be collected and linked to their existing demographic surveillance data, all participants in the two cross-sectional surveys, everyone (health service staff, research staff and community members) who engage in an interview or authorise a consultation to be observed, and all patients completing an exit questionnaire when they leave a clinic.

### Preintervention preparation

First steps in developing plans for the intervention were to carry out literature searches for similar interventions and to meet with local and provincial health service personnel. We then performed a situation analysis in all the local clinics. This involved interviews with clinic staff and collecting and analysing retrospective data on the appointments system and attendance of patients with chronic diseases. We also deployed local trained field workers to conduct nonparticipant observations over a period of 3 days in each clinic. We also held meetings with provincial and district stakeholders and workshops with staff in each clinic to feed back the results of our preparatory work to discuss how the interventions might proceed.

### Study site

The trial is based in the Agincourt subdistrict of Mpumalanga Province, South Africa. This rural area is a former Bantustan, with limited resources, high levels of unemployment and high levels of labour migration [19, 20]. In a population-based survey of 3,729 adults older than 15 years of age in 2010, the prevalence of hypertension was found to be 40% in women and 39% in men, and the prevalence of HIV was 27% in women and 19% in men (unpublished data). There are seven publically funded clinics and one health care centre at the site, plus two clinics just over the border. For this trial, one clinic from the border area, together with the population it serves (a population partly in the HDSS area), will be included as a pilot clinic. The other border clinic will not be considered further. The eight facilities within the site, and with their associated communities, will comprise the clusters. Until recently none of the health facilities kept individual longitudinal patient records. Moreover, individuals are free to use any clinic that is convenient, so, although each clinic has its own catchment area, it is not possible to define a ‘clinic user’ population for each clinic *a priori*.

Since 1992, the MRC/Wits Agincourt Research Unit has collected population data, and vital events (pregnancy outcome, death, migration) are updated yearly [19]. For the purpose of this study, the total population under surveillance is about 90,000 people (52,592 older than 18 years of age) who live in 15,500 households in 26 villages. These census data provide the sampling frame for the planned population surveys and also make it possible to trace patterns of clinic use by identifying clinic users at the facility levels and linking them to the population database. Moreover, the MRC/Wits Agincourt Research Unit provides an administrative research structure to support the trial.

### Intervention and control arms

All eight clinics will continue to implement the government’s ICDM strategy by providing separate care for patients with chronic diseases. In addition, as part of the trial, all clinics will have an attached data clerk responsible for collecting identifiers of all consenting attendees of the chronic disease clinic to allow their identification in the MRC/Wits Agincourt surveillance database. The linked data will enable us to understand patterns of clinic use which may not be geographically determined, as well as differential clinic use associated with sex, age and relative household wealth of clinic users. They will also allow us to monitor whether patterns of clinic use change over the 15 months of the intervention. Previous research [21] has confirmed the key identifiers for posterior links with the census are name, surname, age or date of birth, sex, village of residence, cell phone number, national ID number and name of another person living in the household. The system was piloted successfully in two clinics in 2013 in preparation for the Nkateko trial.

Intervention clinics will also be provided with two full-time lay health workers for 15 months to assist in the management of the patients with chronic diseases, particularly patients with hypertension. Building on experience with lay counsellors in antiretroviral therapy delivery [9], we expect that the lay health workers will provide adherence counselling; help to improve treatment literacy; use text messaging, telephone or personal contacts to remind patients of appointments [22]; and assist with filing of patient records and prepacking of medications. However, the exact roles of the lay health workers will be decided on a clinic-by-clinic basis in workshops run with the clinic staff by the implementation manager, with modification of noncore components to encourage local ownership. Core nonmodifiable components include appropriate staff selection, preservice and in-service training, and staff and programme evaluation. A local experienced nurse has been appointed as the implementation manager who will oversee the selection, introduction and functioning of the lay health workers. We believe this mirrors the type of structure that might be used by a provincial or district health department when introducing such an initiative. The implementation manager is responsible for the development of a functional relationship between the lay health workers and clinic staff, as well as the performance management and evaluation of the lay health workers.

### Study outcomes

We aim to improve the management of hypertension with the goal of achieving a reduction in the proportion of the population with uncontrolled hypertension and a risk profile indicating at least moderate risk of cardiovascular disease. To do this, we aim to both increase the number of people receiving active management of their hypertension and improve the management of blood pressure in those patients already in active management. Because we hope to reach people not currently using the clinics, we have chosen to measure the outcome of the trial at the population level with the use of two population surveys (before and after the intervention).

The primary outcome we will measure is the difference in the change in intervention and control clinics between the two surveys in the proportion of the population who have uncontrolled hypertension and a risk profile indicating at least moderate risk of cardiovascular disease. The definition of this risk profile is shown in Table 1. It reflects the concepts in the 2011 South African guidelines [23], which call for a focus on people at moderate or greater cardiovascular risk. Although the guidelines require clinical diagnoses, we are limited by what is possible in a population survey, so, for the purposes of this trial, we will define the cardiovascular risk factors and associated clinical conditions as outlined in Table 2.

**Table 1 Tab1:** **Modified South African Guideline: stratification of cardiovascular risk in patients with hypertension**
^**a**^

	Presence of risk factors or other conditions			
Blood pressure (mmHg)	No risk factors	One or two risk factors	Three or more risk factors or diabetes	Associated clinical conditions
SBP 140 to 159 or DBP 90 to 99	Low added risk	Moderate added risk	High added risk	Very high added risk
SBP 160 to 179 or DBP 100 to 109	Moderate added risk	Moderate added risk	High added risk	Very high added risk
SBP 180+ or DBP 110+	High added risk	Very high added risk	Very high added risk	Very high added risk

^a^DBP, Diastolic blood pressure; SBP, Systolic blood pressure. Hypertension is defined as SBP >139 mmHg or DBP >89 mmHg.

**Table 2 Tab2:** **Risk factors and associated clinical conditions used for definitions of ‘increased cardiovascular risk associated with hypertension’ in the Nkateko trial**
^**a**^

Risk factors	Associated clinical conditions
Sex/age: men >55 yr, women >65 yr	Self-reported coronary heart disease
Smoking at least every day	Self-reported heart failure
Dyslipidaemia TC >5 mmol/l	Self-reported stroke or TIA
Family history of CVD (sex/age): men <55 yr, women <65 yr	
Waist circumference: men >94 cm, women >80 cm	

^a^CVD, Cardiovascular disease; TIA, Transient ischaemic attack. TC. total cholesterol.

The secondary outcomes of the trial are shown in Table 3.

**Table 3 Tab3:** **Secondary outcomes**

Source	Outcome
Before and after population surveys	Difference in change in proportion of the population with undiagnosed hypertension.
	Difference in change in the proportion of the population reporting they had had their blood pressure measured.
	Difference in change in the proportion of the population reporting they are using medication for hypertension.
	Difference in changes in the proportion of the population at different levels of blood pressure–related cardiovascular risk by age group and sex.
	Difference in change in the proportion of the population reporting they attended a clinic in the past year.
Clinic link with census records	Difference in proportion of population with diagnosed hypertension who are adherent to prescribed medication, defined by recorded collection of prescriptions.
	Difference in retention in care of people with diagnosed hypertension defined by the proportion of appointments kept during the study period.

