### Trial status

Because of the design of the trial, it is difficult to define the status of recruitment. There are eight clinics, four of which receive the intervention and four which do not. They have been randomised, and the lay health workers have been in place since February to March 2014. Although the unit of randomisation is a clinic, the participants could most appropriately be considered to be the people using the clinics. They are participating or declining to participate by consenting to their data being linked to census data and by consenting to complete an exit questionnaire or permit their consultation to be observed as they attend the clinics. In that sense, we are just over halfway through recruitment (10 months of an 18-month period). The outcome is measured by population surveys at baseline and at the end of the intervention. If the people in those surveys are considered to be the participants, then we have recruited half (one survey). A separate group of around the same number of people will be asked to complete the survey at the end. The trial status was most recently updated 6 November 2014.

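### Retention in care is defined by appointments kept, a measure that largely hides patients who drop out

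*Protocol article*

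**What the plan says.** Table 3 takes two secondary outcomes from the clinic records linked to the census. One is adherence, judged by recorded prescription collection among people with diagnosed hypertension. The other is "Difference in retention in care of people with diagnosed hypertension defined by the proportion of appointments kept during the study period". The table does not say whether the denominator is visits booked or visits due, whether the proportion is pooled or averaged over patients, or how a patient with no further booking counts. It does not define the study period.

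Retention matters to the trial's argument. Under Research hypothesis and objectives, the lay health workers are expected to improve population-level management "by improving diagnosis, retention in care and adherence to treatment by individuals with hypertension". The Background says that "long-term patient retention is low".

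Under Intervention and control arms, the lay health workers are expected to counsel on adherence, improve treatment literacy, "use text messaging, telephone or personal contacts to remind patients of appointments" and "assist with filing of patient records and prepacking of medications". Their exact roles are settled separately in each clinic. Helping to trace defaulters appears only in the Background, as earlier lay-worker experience in South Africa. Advance booking belongs to the national chronic disease programme, of which the Background says: "The ICDM programme is already operational to a varying extent in the eight clinics in which this trial is being implemented".

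Of the linked data, Intervention and control arms says: "They will also allow us to monitor whether patterns of clinic use change over the 15 months of the intervention".

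**The concern.** Retention is a property of a person over time: is the patient still in care? The ratio in Table 3 is a property of appointments. Someone who leaves and is not rebooked generates no more appointments, so an absence of one month and an absence of a year cost the same single missed visit. The measure is least sensitive to the failure that the Background names and the hypothesis sets out to reduce.

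The denominator may also respond to the intervention. If an intervention clinic brings irregular attenders back, their further bookings enter the ratio, and each one missed lowers it. Booking practice may differ between clinics as well: the chronic disease programme runs to differing degrees, and the process evaluation's exit interview has to ask whether a return visit was booked. At stake is the reading of one of the three pathways in the hypothesis. A real gain in retention could appear as little change, or even as a loss.

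**Working it through.** The Protocol article gives no figure for this outcome, so there is none to reproduce. It gives no dropout, booking or attendance rates either. Only the 15 months come from the document (Intervention and control arms). Every rate below is an assumption, and monthly appointments are used only to keep the arithmetic simple.

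**1. One patient.** A patient keeps 4 visits, misses the fifth and is not rebooked. Kept/booked = 4/5 = 80%. Over 15 visits due, kept/due = 4/15 = 27%. A patient who stays throughout and keeps 85% of visits scores 85% on both. The two patients differ by 5 points on the first measure and 58 on the second.

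**2. Dropout without rebooking.** Let a fraction d of those in care miss a visit each month and leave, with all other visits kept.
- Still in care at month 15: (1 − d)^15.
- Kept/booked: 1 − d in every month, however long the follow-up.
- Kept/due: (1 − d)[1 − (1 − d)^15]/(15d).

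| d | in care at 15 months | kept/booked | kept/due |
|---|---|---|---|
| 2% | 74% | 98% | 85% |
| 5% | 46% | 95% | 68% |
| 10% | 21% | 90% | 48% |

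Cutting monthly dropout from 5% to 2% raises retention by about 28 points and kept/booked by 3.

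**3. Dropouts brought back.** Keep d = 5%, but rebook every absent patient monthly, with 25% returning each time. Then p(t) = 0.95p(t−1) + 0.25[1 − p(t−1)], with p(0) = 1, so p(t) = 0.833 + 0.167 × 0.70^t. In care at month 15: 83%. Kept/booked, the mean of p(t) over 15 months: 86%. Compared with the 5% row above, retention rises from 46% to 83% while kept/booked falls from 95% to 86%. This model gives reminders no effect and assumes perfect attendance before dropout, so it favours a reversal.

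**4. A less one-sided model.** There are 100 patients per arm and 15 visits due each. Sixty stay and keep 85%. Forty keep m = 4 visits, miss one and get no further booking. In the intervention arm, half of those forty are brought back for the remaining 10 visits and keep a share r = 0.6.
- Control: kept = 60×15×0.85 + 40×4 = 925; booked = 60×15 + 40×5 = 1,100; ratio 84.1%.
- Intervention: kept = 765 + 20×4 + 20×(4 + 10×0.6) = 1,045; booked = 900 + 20×5 + 20×15 = 1,300; ratio 80.4%.
- Kept/booked therefore falls by 3.7 points.
- Kept/due: 925/1,500 = 61.7% against 1,045/1,500 = 69.7%, up 8.0 points.
- Still under booking: 60% against 80%.

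**5. How far the sign depends on the inputs.** Bringing patients back raises the pooled ratio only if r exceeds the control ratio: 83.5%, 84.1% and 85.2% for m = 3, 4 and 6. For r from 0.5 to 0.8 the pooled ratio falls by 0.6 to 5.8 points, while kept/due rises by 5 to 12. At r = 0.9 it rises slightly. If reminders also lift attendance among those who stay from 85% to 92% (m = 4, r = 0.6), kept = 828 + 80 + 200 = 1,108, and 1,108/1,300 = 85.2% exceeds 84.1%. The break-even attendance is (0.841×1,300 − 280)/900, about 90.4%.

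**The case against.** The strongest reply is that Table 3 does not say booked. If every visit due stays in the denominator, dropouts count and step 4 shows no reversal. A condensed article may leave such detail to the full protocol and to the analysis plan promised under Data management and analysis. The ambiguity is real, and omitting operational detail is not in itself a fault. But the table does fix the definition as a proportion of appointments, and a patient with no further booking has no appointments to count. Making dropouts count needs a fixed set of people or a schedule of visits due, and the stated definition contains neither.

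A reader might infer that the lay health workers are there to trace and rebook defaulters, so that the outcome will run backwards. The document does not support this. Neither task is listed, and advance booking is part of a programme running in all eight clinics. The open role makes tracing possible, nothing more. Reminders are listed, and the ratio rewards them.

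A reader might also infer that the study period is 18 months, leaving three months without lay workers. The 18 months under Trial status describe recruitment in a loose sense and do not define the period in Table 3. The linked data are tied to the 15 months.

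Dropout is not invisible elsewhere: prescription collection, survey-reported clinic attendance in the past year and medication use would each reflect some of it. This limits the harm, but none of them is the outcome named retention.

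**Conclusion.** The point stands as a weakness in the stated definition of one secondary outcome. On the plain reading, the measure barely responds to dropout: under an assumed 5% monthly rate it shows 95% while 46% remain in care. This needs no assumption about what lay health workers do, only that appointments cease when a patient leaves and is not rebooked. A reversal between arms is possible under plausible inputs (84.1% against 80.4% in the worked case), but it rests on assumed rates, on a booked-appointment denominator and on dropouts being brought back. It is not a prediction. The primary outcome, measured in population surveys, is unaffected.

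**What to change.** Redefine the outcome per person, in the analysis plan and before analysis:
- **Denominator:** consenting patients with diagnosed hypertension, each entering at the first linked visit in the intervention period, over the same calendar months in both arms. Do not use a cohort already known at the start. The Discussion says individual records were absent until very recently and then of variable quality, and such a cohort would exclude newly diagnosed patients, whom the trial hopes to reach.
- **Retained:** a clerk-logged chronic-care attendance, other than the entry visit, at any of the eight clinics in the final interval. Alternatively, report the share of 3-month intervals with an attendance. Patients with no further contact count as not retained. Fix the interval length in advance and check it against usual visit spacing, which the article does not give.
- **Period:** state that the study period is the 15-month lay-worker period.
- **Process measure:** report appointments kept separately, with its denominator stated.

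The cost is the rewording of one secondary outcome, provided the clerks already in all eight clinics record visit dates, as tracking patterns of clinic use implies. Limits remain: attendance outside the eight clinics and by non-consenting patients is not seen, late entrants have shorter follow-up, and who enters may still differ between arms, so entrants should be described by arm.
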